**Other secondary outcomes**	
Communication and Daily Living Skills domain of the Vineland Adaptive Behavior Scales, 3rd edition (VABS−3) (26).	The Communication and Daily Living Skills domains of the VABS-3 (described in primary outcome above) will be administered to assess these areas of adaptive behavior.
Brief Observation of Social Communication Change (BOSCC) (30)	The BOSCC is a brief, 12-min observation of a semi-structured social interaction between the participant and an examiner. The interaction is video-recorded, and autism symptoms are coded using an algorithm.
Social Responsiveness Scale, 2nd edition (SRS−2) (31)	The SRS−2 is a 65-item measure identifying the presence and severity of autistic symptoms. Items are rated on a 4-point scale with higher scores reflecting more severe autism. It will be completed by parents/carers and teachers. The teacher completing this measure should spend at least 10 h per week in direct contact with the participant.
Autism Impact Measure (AIM) (32)	The AIM will be completed by the parent/carer to assess symptoms of autism. It consists of 41 items measuring both the frequency and impact of autism symptoms using a 5-point scale.
Aberrant Behavior Checklist - Community version (ABC-C) (24)	The ABC-C will also be completed by the parent/carer to measure irritability, lethargy/social withdrawal, stereotypic behavior, hyperactivity/non-compliance, and inappropriate speech displayed by the participant. Fifty-eight items are rated on a 4-point scale, with higher scores indicating more severe problem behaviors. The ABC-C will be completed by the parent/carer.
Child Behavior Checklist (CBCL) (33)	The CBCL will be used to measure emotional and behavioral problems. Items are rated on a 3-point scale with higher scores indicating more problems. Two different versions will be administered to parents of 5-year olds (1–5-year version) and 6–17-year olds (6–18-year version).
Pediatric Quality of Life Inventory (PedsQL) (34)	The PedsQL measures health related quality of life in children and adolescents. The Generic Core Scales, consisting of 23 items rated on a 5-point scale, will be used to measure physical and psychosocial health. Parents/carers will complete one of three different versions dependent on the participant's chronological age (5–7; 8–12; 13–18 years).
**Exploratory measures**	
Electrophysiology and sensory processing	Electrophysiology and sensory processing will be measured using electroencephalograms (EEG). Computer tasks chosen specifically for the trial will be completed whilst the EEG is being conducted to measure resting state, response to social and non-social stimuli, auditory processing and habituation response. The tasks take about 1 h to complete.
DNA acquisition	DNA samples (using 6 mls EDTA tubes) will be obtained from patient, and both parents when possible. This will help us to explore the genetics of those responders to the drug, vs. non-responders.
Digital Biomarkers	Digital biomarker (dBM) technology allows the remote measurement of the signs and symptoms of ASD, which can potentially reduce the burden of site visits and allow frequent/daily tracking in an ecologically valid environment. Patients will be asked to complete some tasks on a pre-set mobile phone and wear a smart wrist watch during the time of the study. Bluetooth beacons will be used to estimate the frequency of social interactions at home.
**Safety assessments**	
Medical checks	Vital signs (pulse, temperature and non-supine blood pressure) will be checked by a treating clinician. Physical examinations and electrocardiograms will be performed, and height and weight will be recorded with all outer wear and shoes removed. Safety blood tests checking complete blood count, liver enzymes, renal function and non-fasting glucose will be performed. Pregnancy testing will be performed for female participants of childbearing potential. Drug testing will also be performed on urine samples.
Safety Monitoring Uniform Report Form (SMURF) (35)	The SMURF will be administered by a treating clinician to record possible adverse events of psychotropic medication. Where appropriate, the participant and their parent/carer will be interviewed together and events since the last visit will be sought.
Epworth Sleepiness Scale for Children and Adolescents (ESS-CHAD) (36)	The ESS-CHAD will be administered by a treating clinician to measure daytime sleepiness and sedation in the past week. It consists of 8 items tapping into different situations which are rated on a 4-point scale with higher scores indicating greater chance of sleepiness.
Columbia-Suicide Severity Rating Scale (C-SSRS) (37)	Suicidality assessments will be completed by a treating clinician using the C-SSRS to measure the presence and intensity of suicidal ideation and behavior. The “baseline” version will be administered at week 0 and the “since last time” version thereafter. Two different versions will be administered depending on the chronological age of the participant.
**Screening/characterization assessments**	
Autism Diagnostic Observation Schedule−2 (ADOS−2) (27)	The ADOS−2 modules 3 or 4 will be administered to enable characterization of autism symptoms and severity. If a reliable ADOS−2 assessment has been administered in the 24 months prior to screening, with family consent, the scores from the previous assessments will be used an administration of these assessment will not be required.
Wechsler Scales	The appropriate Wechsler Scales according to age will be administered to enable characterization of the cognitive functioning of the sample. If a reliable standardized cognitive assessment has been administered in the 24 months prior to screening, with family consent, the scores from the previous assessments will be used an administration of these measures will not be required.
Social Communication Questionnaire-Lifetime version (SCQ) (38)	The SCQ is a 40-item yes-no measure of autism symptoms and severity and will be completed by the parent/carer. Scores of 15 or greater indicate a possible ASD.
Repetitive Behavior Scale-Revised (RBS-R) (39)	This questionnaire is part of the digital biomarkers optional sub-study and only completed if opted in. The RBS-R is an empirically-derived comprehensive survey of the entire spectrum of repetitive behaviors clinically observed and referred to in the DSM-IV (3) diagnostic description of Autistic Disorder. Parents or caregivers rate 43 behaviors on a scale of 0–3, where 0 indicates the behavior does not occur and 3 indicates the behavior does occur and is a severe problem.

### Sample Size

Based on Veenstra-VanderWeele et al. (23), for a 5.3 (standard deviation of 15) change from weeks 0 to 16 in scores on the VABS−3 Socialization domain for those treated with arbaclofen vs. placebo, 100 participants are needed in each arm, assuming 2-sided testing at a significant level of 5 and 80% power. Allowing for 10% attrition, the total sample required would be 220, 110 in each treatment arm. Therefore, the sample from this study will be combined with that of the Canadian ARBA trial to attempt to answer to the key objective. AIMS-CT1 will recruit 130 participants across the seven study sites (i.e., ~19 participants each) and ARBA-Brain Canada will recruit 90 participants.

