### Randomization and Allocation

Randomization of participants will be performed 1:1 into arbaclofen vs. placebo by a randomization website (Interactive Web Response System—IWRS) developed by the Data Management Department of the Julius Center, University Medical Center Utrecht (UMCU). Allocation will be sent to an unblinded dedicated pharmacist at each individual site as specified in a separate Pharmacy Manual. A central unblinded monitor will double check dispensation regularly. The rest of the study members are blind to allocation. Randomization will be stratified by site and age group (5–11 years old; 12–17 years old). Unblinding will only happen if the information can help treat an adverse event and for safety reasons.

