### Statistical Analysis

Analysis will be performed both with an Intent to Treat (ITT) and as Per Protocol (PP) approach. The initial efficacy analysis will use the ITT sample, which includes all participants randomized who have at least one dose of medication and one post-baseline assessment. To be included in the PP sample, participants will fulfill ITT criteria and have attended at least 80% of the visits, have taken at least 70% of the prescribed medication and have a consistent pre- and post-intervention VABS−3 clinician rater.

Efficacy will be indicated by a difference between treatment arms at week 16, using Analysis of Covariance (ANCOVA; with follow-up score used as the dependent variable and treatment group as a factor) or logistic regression, and Chi-Square techniques, as appropriate. Age will be adjusted for and baseline scores will be used as covariates. Hypothesis testing will be performed at the 5% level of significance for 2-sided tests. Safety analyses will be conducted on all participants taking at least one dose of study medication by calculating the incidence of adverse events in each arm and summarizing laboratory and ECG assessments, physical examinations and vital signs.

A secondary analysis will be conducted by combining data from AIMS-CT1 and the ARBA Study to ensure statistical power for the assessment of efficacy of the primary outcome variable. Additional analyses will consider variables or sub-variables that will be different from or derivative of the primary and secondary hypotheses. Another level of analysis will look at data of individual sites. Power calculation was made for the primary outcome (VABS-3 social function domain), which justifies the a priori planned combination of the data of this study with that of ARBA Study in Canada. Other results will be considered secondary results and therefore more exploratory and hypotheses-generating.

While no interim analysis is planned, if necessary, the Data Monitoring Committee (DMC) will consider it and inform the Sponsor whether premature termination criteria are met.

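### The stated inputs for the sample size give 126 to 127 per arm at two-sided 5%, not 100; at 100 per arm the calculation as stated has about 70% power, not 80%

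*Protocol article*

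**What the plan says.** All the inputs are in the protocol article.

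- **Effect and SD** (Sample Size): the calculation is "for a 5.3 (standard deviation of 15) change from weeks 0 to 16 in scores" on the VABS-3 Socialization domain, arbaclofen against placebo.
- **Result** (Sample Size): "100 participants are needed in each arm, assuming 2-sided testing at a significant level of 5 and 80% power". The percent sign after the 5 is missing, but the Statistical Analysis section supplies it.
- **Attrition** (Sample Size): "Allowing for 10% attrition, the total sample required would be 220, 110 in each treatment arm".
- **Use of the figure** (Sample Size): the 220 is the stated reason for combining this trial with the Canadian ARBA study. "AIMS-CT1 will recruit 130 participants across the seven study sites" and ARBA contributes 90, so 130 + 90 = 220.
- **Allocation** (Randomization and Allocation): "Randomization of participants will be performed 1:1 into arbaclofen vs. placebo".
- **Planned test** (Statistical Analysis): "Hypothesis testing will be performed at the 5% level of significance for 2-sided tests". The model is ANCOVA on the follow-up score, and "Age will be adjusted for and baseline scores will be used as covariates".

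The Statistical Analysis section also says that the combined analysis is there to secure power for the primary outcome, and that the power calculation justifies the combination. The article gives no baseline to follow-up correlation and mentions no variance reduction in the sample size.

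**The concern.** A standardised difference of 5.3/15, about 0.35, at two-sided 5% and 80% power calls for clearly more than 100 per arm. The gap of 26 to 27 per arm is about one fifth of the number required, so rounding or the choice between a normal and a t calculation cannot explain it.

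This is the only power statement for the primary outcome in the article. The total of 220 and the argument for combining two trials both follow from it. If it is wrong, the article claims more power for the pooled comparison than its own inputs support: on those inputs the type II error is about 30%, not 20%.

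**Working it through.** **Inputs.** Difference 5.3 and SD 15 (Sample Size); two-sided 5% (Sample Size and Statistical Analysis); 80% power (Sample Size); 1:1 allocation (Randomization and Allocation). The standardised difference is 5.3/15 = 0.3533, and its square is 0.1248.

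**Step 1: try to reproduce 100 per arm.** For an unadjusted comparison of two means,

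n per arm = 2 × (z_alpha + z_power)² / (difference/SD)².

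- Two-sided 5%: 2 × (1.960 + 0.8416)² / 0.1248 = 125.7, so **126** (t test: **127**).
- One-sided 5%, the same as two-sided 10%: 2 × (1.645 + 0.8416)² / 0.1248 = 99.04, so **100** (t test: also 100).

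The stated two-sided inputs do not reproduce the figure. The one-sided variant reproduces it exactly.

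**Step 2: power at 100 per arm.** The noncentrality is 0.3533 × √(100/2) = 2.498.

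- Two-sided 5%: Φ(2.498 − 1.960) = 70.5%; t test **70.1%**.
- One-sided 5%: Φ(2.498 − 1.645) = 80.3%; t test 80.1%.

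**Step 3: difference detectable with 80% power at 100 per arm, two-sided 5%.** 15 × (1.960 + 0.8416)/√50 = 5.94; t test 5.97. That is about **6.0** points, not 5.3.

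**Step 4: what the planned ANCOVA could change.** Let r be the correlation between baseline and week 16. It is not in the article, so it is an assumption here, as is equal variance at the two times. Only the residual SD in the formula changes.

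- If 15 is the SD of the score, the residual SD is 15 × √(1 − r²).
- If 15 is the SD of the change, then SD_change² = 2σ²(1 − r), where σ is the SD of the score. The residual variance σ²(1 − r²) equals SD_change² × (1 + r)/2, so the residual SD is 15 × √((1 + r)/2).

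Two-sided 5% power at 100 per arm for a difference of 5.3 (t test):

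| r | 15 is SD of score | 15 is SD of change |
|---|---|---|
| 0.3 | 74% | 87% |
| 0.5 | 82% | 82% |
| 0.7 | 94% | 77% |
| 0.8 | 99% | 75% |

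Power reaches 80% when r is **at least about 0.46** on the first reading and **at most about 0.57** on the second. The normal approximation puts these limits at about 0.45 and 0.59.

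**The case against.** The strongest reply is that the trial will not run the unadjusted test. The Statistical Analysis section fixes ANCOVA with baseline as covariate. On either reading of SD 15 and for any non-negative r, its power at 100 per arm is about 70% or higher, and for r between about 0.46 and 0.57 it reaches 80% on both readings. This stands. A reader might infer that the pooled analysis has only 70% power; the article does not support that, because the power of the planned model cannot be fixed without r. Nor does ANCOVA help only if 15 is the SD of the score: the table shows a gain on the SD-of-change reading too.

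The reply does not rescue the figure, however. The Sample Size section gives no correlation and claims no covariate adjustment. The two readings of SD 15 also set opposite conditions on r, so the reader cannot supply the missing step.

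A reader might also conclude that the calculation was in fact run one-sided. The exact match makes that plausible, but it is an inference. Two-sided 10% gives the same 100, and an ANCOVA on a score SD of 15 with r near 0.46 would also give about 80%. The full protocol, which might show the source, is not available. The mismatch does not depend on its origin.

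Finally, it is tempting to say that a null pooled result would be over-read. The article sets no rule for interpreting a null result, presents pooling as an attempt to answer the question, and labels the combined analysis secondary. The demonstrable point is that the stated power does not follow from the stated inputs.

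**Conclusion.** Wrong as written. On its own inputs the Sample Size section should report 126 evaluable per arm (t test 127), not 100. As stated, 100 per arm gives about 70% two-sided power for 5.3 points, and 80% only for about 6.0. The figure conflicts with the two-sided 5% testing fixed in both sections, and nothing in the article reconciles it.

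The size rests on an unadjusted comparison of two equal arms with SD 15. It describes the published calculation, not the planned ANCOVA, whose power remains open until the type of SD and the correlation are stated. The limits of 0.46 and 0.57 assume equal variances at baseline and week 16.

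**What to change.** Correct the Sample Size section in one of two ways, with no change to enrolment:

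- **(a)** State that 100 evaluable per arm in the pooled sample gives about 70% power for a difference of 5.3 (SD 15), or 80% for about 6.0, at two-sided 5% without covariate adjustment.
- **(b)** If the ANCOVA is to justify 100 per arm, say whether 15 is the SD of the score or of the change, state the assumed baseline to week-16 correlation and its basis, and give the ANCOVA power over a range of correlations.

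Then amend the sentence in the Statistical Analysis section saying that pooling secures power, so that it matches the corrected figure.

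The cost is wording only, and the stated power may become less favourable. If the sponsor instead requires 80% for 5.3 with no covariate credit, 126 to 127 evaluable per arm are needed: 126/0.9 = 140 and 127/0.9 = 141.1, rounded up to 142, so 280 to 284 in total with 10% attrition. Whether to enlarge the sample is the sponsor's decision; this correction does not depend on it.

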### Recruitment

Recruitment of participants will be through referral via local autism diagnostic teams and pediatric and Child and Adolescent Mental Health Services at each study site. Consent databases/registers, support groups and advertisements on relevant websites may also be used. Potential participants can also self-refer. After initial contact by attending physician, and provided the participant/legal tutor give consent to be contacted, a study member will contact with the parent/carer and potential participant for pre-screening for eligibility, and, if appropriate, families will be invited to attend a screening visit to be assessed for eligibility and discuss consent. Principal investigator or delegated research team physicians will explain and subsequently obtain informed consent/assent. If patient/family agrees to participate, a schedule for the whole trial will be agreed with them, in order to accommodate families' needs and availability and make the completion of the trial more plausible. Privacy laws and regulations will be adhered to during all procedures related to this study. The collection and processing of participants' personal information will be limited to what is necessary to insure the study's scientific practicability. The local investigator or her/his co-workers will collect data and transfer it without recording the patient's name or date of birth coded with a patient identification number. A patient identification code list linking the individual patients to the identification numbers will be kept at the site; access is restricted to authorized study team members.

### Assessments

Table 3 shows the schedule for enrolment, treatment and the visits for participants, including all the assessments conducted at each visit. Participation in the trial will consist of a screening visit followed by eight visits for a period of 18 weeks. Table 3 shows an overview of the timeline and specific assessments conducted at each visit. To check the adherence, the left over pills get accounted for at all visits and crosschecked with the compliance calendar for medicine intake given to the families.

**Table 3 T3:** Participant timeline showing schedule of enrolment, treatment and visits for participants.

[figure not shown]

*Columns shaded in gray are the face-to-face visits. ABC-C, Aberrant Behavior Checklist-Community; ADOS−2, Autism Diagnostic Observation Schedule, 2nd edition; AIM, Autism Impact Measure; BOSCC, Brief Observation of Social Communication Change; CBCL, Child Behavior Checklist; CGI-S, Clinical Global Impression-Severity; CGI-I, Clinical Global Impression-Improvement; C-SSRS, Columbia-Suicide Severity Rating Scale; ECG, Electrocardiogram; EEG, Electroencephalogram; ESS-CHAD, Epworth Sleepiness Scale for Children and Adolescents; PC, Phone call; PedsQL, Pediatric Quality of Life Inventory SC, Screen; SCQ, Social Communication Questionnaire; SMURF, Safety Monitoring Uniform Report Form; SRS−2, Social Responsiveness Scale, 2nd edition; VABS−3, Vineland Adaptive Behavior Scales, 3rd edition*.

* *optional [the digital biomarkers include the completion of one small cognitive task every day, the completion by the parent of the RBS-R questionnaire (39) at visits 1 and 7, and the completion of satisfaction questionaries at visit 7; for DNA, samples will be also collected from both parents if applicable]*.

The trial includes a targeted electroencephalogram (EEG) battery designed to capture sensitive and predictive biomarkers of treatment efficacy at a level that is putatively closer to the underlying neural systems affected by arbaclofen. EEG measures the coordinated electrical activity of pyramidal cells in the outer cortical layers (40).

The task battery (see Additional Material 1 for full information) is designed to tap potential electrophysiological effects of arbaclofen on the (1) excitatory-inhibitory balance of cortical neural activity, and (2) brain specialization for social processing that may relate to the social functioning targeted in the trial, manifested by brain responses to social stimuli (41, 42).

An optional blood sample for DNA extracting is collected from participants and his/her parents that specifically consent to this. Samples are then sent for analyses to Institut Pasteur (Paris, France) where is and safely stored for 25 years after the explicit consent of the patient/legal/parents with a personal code with no connection with any personal information. Also optional, is the inclusion of digital biomarkers (see Additional Material 1), to obtain pilot evidence for treatment responsive biomarkers relevant to core and associated symptoms of autism.

All the procedures undertaken and all relevant clinical information is collected both in the electronic CRF and the electronic medical record.

### Statistical Analysis

Analysis will be performed both with an Intent to Treat (ITT) and as Per Protocol (PP) approach. The initial efficacy analysis will use the ITT sample, which includes all participants randomized who have at least one dose of medication and one post-baseline assessment. To be included in the PP sample, participants will fulfill ITT criteria and have attended at least 80% of the visits, have taken at least 70% of the prescribed medication and have a consistent pre- and post-intervention VABS−3 clinician rater.

Efficacy will be indicated by a difference between treatment arms at week 16, using Analysis of Covariance (ANCOVA; with follow-up score used as the dependent variable and treatment group as a factor) or logistic regression, and Chi-Square techniques, as appropriate. Age will be adjusted for and baseline scores will be used as covariates. Hypothesis testing will be performed at the 5% level of significance for 2-sided tests. Safety analyses will be conducted on all participants taking at least one dose of study medication by calculating the incidence of adverse events in each arm and summarizing laboratory and ECG assessments, physical examinations and vital signs.

A secondary analysis will be conducted by combining data from AIMS-CT1 and the ARBA Study to ensure statistical power for the assessment of efficacy of the primary outcome variable. Additional analyses will consider variables or sub-variables that will be different from or derivative of the primary and secondary hypotheses. Another level of analysis will look at data of individual sites. Power calculation was made for the primary outcome (VABS-3 social function domain), which justifies the a priori planned combination of the data of this study with that of ARBA Study in Canada. Other results will be considered secondary results and therefore more exploratory and hypotheses-generating.

While no interim analysis is planned, if necessary, the Data Monitoring Committee (DMC) will consider it and inform the Sponsor whether premature termination criteria are met.

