### Participants

#### Inclusion Criteria

Male and female participants aged between 5:0 and 17:11 years at time of consent, with a diagnosis of ASD according to the DSM-5 (3) criteria and complex verbal language [defined as qualifying for an Autism Diagnostic Observation Schedule−2 (ADOS−2) Module 3 or 4 assessment (27), as determined by a clinically-certified ADOS-2 rater supervised by the local research-reliable ADOS-2 lead (see Requirements in Additional Material 5)].The parent/carer (hereafter parent; for brevity) can speak and understand the local language.The participant resides with the parent who will complete the primary outcome.Willingness to comply with the medication and research protocols.Pharmacological treatment affecting behavior stable for at least 6 weeks prior to screening, with no planned changes for the duration of the trial.Psychotherapeutic/psychosocial interventions affecting behavior stable for at least 3 months prior to screening, with no planned changes for the duration of the trial.Seizure history stable with anticonvulsant medication and seizure free for at least 6 months prior to screening. If anticonvulsant medication has not been stable for at least 3 months, the participant must be seizure free for at least 3 years prior to screening.Negative pregnancy test for female participants of childbearing potential.Female participants, and female partners of male participants, who are of childbearing potential and sexually active must agree to use highly effective forms of contraception.Participant able to take medication orally.

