**Primary outcome**	
Socialization domain of the Vineland Adaptive Behavior Scales, 3rd edition (VABS−3) (26)	The Socialization Domain of the VABS−3 measures social function and behavior, covering interpersonal relationships, play and leisure and coping skills. The informant (parent/carer) is required to reside with the participant. The same informant and interviewer will be used at both timepoints, and any change will be reported as a protocol deviation, and wherever possible the interviewer will be blind to other study assessments. Interviewers administering the VABS−3 will be required to achieve 90% reliability with a gold standard rater in order to administer it for the trial. Regular reliability meetings will be scheduled for VABS−3 gold standard raters and interviewers across study sites to maintain reliability.

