Design of the current trial was informed in two important ways by lessons learnt from the Veenstra-VanderWeele et al. (23). First, the primary outcome is the Socialization domain of the VABS−3 (26). Following results in Veenstra-VanderWeele et al. all efforts will be made to maintain the same interviewer and informant at both time points and any change in interviewer or informant will be reported as a protocol violation. When possible, the VABS−3 rater will be blind to other study assessments, otherwise this will be considered a protocol deviation. All interviews will be recorded for external monitoring, with a central gold standard rater per site that will review at least 25% of the recordings and provide feedback to raters. Specific training was provided within the trial team across sites to address the particular challenges of conducting an international study conducted in multiple languages, and the trial team consulted with a co-author ([name]) of the instrument on training on the VABS−3.

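### The per-protocol set requires the same VABS-3 rater but not the same informant, although the protocol requires both and gives a change in either the same status

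*Protocol article*

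**What the plan says.** The PP set is defined under Statistical Analysis in one sentence. It opens "To be included in the PP sample, participants will fulfill ITT criteria and have attended at least 80% of the visits" and goes on to require that participants "have taken at least 70% of the prescribed medication and have a consistent pre- and post-intervention" VABS-3 clinician rater. The ITT criteria that it builds on cover a sample that "includes all participants randomized who have at least one dose of medication and one post-baseline assessment". Neither definition mentions the informant.

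Two other places set the rule for the primary outcome:

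- Table 2, Primary outcome: "The same informant and interviewer will be used at both timepoints, and any change will be reported as a protocol deviation".
- Discussion, on lessons from the earlier arbaclofen trial: "any change in interviewer or informant will be reported as a protocol violation".

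Table 2 also states who the informant is: "The informant (parent/carer) is required to reside with the participant". The Inclusion Criteria add: "The participant resides with the parent who will complete the primary outcome".

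**The concern.** The VABS-3 Socialization score is obtained by interviewing a parent or carer, so the informant is the source of the data just as the interviewer is its recorder. A switch of either puts between-person differences into the baseline-adjusted week 16 comparison. The protocol recognises this by pairing the two in its conduct rules, but only the rater half of the pair reaches the PP definition.

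Take a child described by one parent at week 0 and by the other at week 16, with the same interviewer and adequate visits and medication. That child meets every PP criterion and is also a reportable violation on the primary endpoint.

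The PP analysis is likely to be read with attention. The Background reports that the earlier trial's Vineland Socialization signal came from a per-protocol, same-clinician analysis, and the Outcomes section says that the primary outcome was chosen following that trial's post-hoc findings.

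**Working it through.** **1. The criteria against the conduct rule.**

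| Requirement | Conduct rule (Table 2, Discussion) | PP criterion (Statistical Analysis) |
|---|---|---|
| Same VABS-3 interviewer at both timepoints | Yes; a change is reported | Yes |
| Same VABS-3 informant at both timepoints | Yes; a change is reported, with the same status | Not mentioned |

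Table 2 calls either change a deviation and the Discussion calls either change a violation. Within each place the two changes rank equally, so the mismatch exists under both labels.

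**2. Whether another rule closes the gap.** The inclusion criterion requires the child to live with the parent who completes the primary outcome. Two co-resident parents could both satisfy it, so it does not rule out a switch. The section on COVID adjustments keeps the same rater and informant for videoconference assessments, but this governs conduct and not membership of an analysis set. Neither removes a participant with a changed informant from the PP set.

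**3. How many participants.** The article gives no rate of informant change. With 130 participants and the 10% attrition in the Sample Size section, 130 × 0.9 = 117 complete. An assumed 5% is 117 × 0.05 = 5.85, about 6 participants; an assumed 10% is 117 × 0.10 = 11.7, about 12.

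**4. Effect on precision.** All inputs here are assumptions: a fraction c = 5% or 10% with a changed informant; baseline to week 16 correlation r_s = 0.7 or 0.8 with the same informant and r_c = 0.4, 0.5 or 0.6 with a changed one; equal variances; one pooled ANCOVA slope; the age covariate ignored.

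- Pooled correlation: r = (1 − c)·r_s + c·r_c
- Residual SD, keeping all relative to same-informant pairs only: √[(1 − r²)/(1 − r_s²)]
- SE(keep)/SE(exclude) = that ratio × √(1 − c), because exclusion shrinks the sample by the factor 1 − c

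Worked example, r_s = 0.7, r_c = 0.6, c = 10%: r = 0.9 × 0.7 + 0.1 × 0.6 = 0.69. The SD ratio is √(0.5239/0.51) = 1.0135, and the SE ratio is 1.0135 × √0.9 = 0.9615.

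| r_s | r_c | SD ratio, c = 5% | SE ratio, c = 5% | SD ratio, c = 10% | SE ratio, c = 10% |
|---|---|---|---|---|---|
| 0.8 | 0.4 | 1.043 | 1.017 | 1.083 | 1.028 |
| 0.8 | 0.5 | 1.033 | 1.006 | 1.063 | 1.009 |
| 0.8 | 0.6 | 1.022 | 0.996 | 1.043 | 0.989 |
| 0.7 | 0.4 | 1.020 | 0.994 | 1.040 | 0.986 |
| 0.7 | 0.5 | 1.014 | 0.988 | 1.027 | 0.974 |
| 0.7 | 0.6 | 1.007 | 0.981 | 1.014 | 0.962 |

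The residual SD ratio runs from 1.007 to 1.083 and the SE ratio from 0.962 to 1.028. In 8 of the 12 scenarios the SE ratio is below 1, so keeping these participants gives the smaller standard error. At the extremes, exclusion raises the SE by 1/0.9615 − 1 = 4.0% or lowers it by 1 − 1/1.0276 = 2.7%.

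**The case against.** The strongest reply is that nothing in the article says a PP set must exclude every reportable deviation. Table 2 and the Discussion say that changes are reported, not that they lead to exclusion, and PP sets commonly exclude a chosen subset. The Discussion also makes a VABS-3 rater who is not blind to other assessments a deviation, and the PP rule does not exclude that either. The rater-only rule has a visible origin too: the earlier signal was a same-clinician result, and the Background says nothing about informants. Finally, informant consistency is already pursued in conduct, so few participants may be affected, and the full protocol or SAP may hold finer PP criteria.

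Part of this stands. The choice of exclusions is a design judgement, the number may be small, and a document not shown may settle the matter. But the article states its PP criteria specifically and takes up one half of a pair that it otherwise treats as equal. The unblinded rater is not a full parallel, because the Discussion calls that a deviation and an informant change a violation. If a fuller document has the informant criterion, the article's definition still needs to be brought into line.

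A reader might infer that the PP estimate would be biased, or that excluding these participants would sharpen it. The documents support neither. They give no reason why informant changes should differ between arms in a double-blind trial, and the scenarios above show that exclusion loses precision more often than it gains it.

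**Conclusion.** The inconsistency is real and minor. The PP definition, taken as written, keeps participants whom the protocol itself would report for a change in the source of the primary outcome, while it removes those with the equivalent change of rater. This rests on the text alone and needs no assumption.

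Its size cannot be fixed from the article: the 6 to 12 participants and the SE change of about +4% to −3% depend wholly on the assumed rates and correlations. The initial efficacy analysis uses the ITT sample, so only the supporting analysis is affected.

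A reader might also take the added criterion to make the PP set free of all deviations on the endpoint. It would not, since an interviewer not blind to other assessments would still be included. The benefit is a PP set that agrees with the protocol's own paired rule for interviewer and informant.

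**What to change.** Extend the PP definition so that, besides the existing conditions, a participant must have the same VABS-3 informant at week 0 and week 16. Settle this before unblinding, so that membership is not decided with results in view. If the omission is deliberate, state why an informant change is tolerated when a rater change is not. Use one label, deviation or violation, for such a change in Table 2 and the Discussion. Keep these participants in the ITT analysis.

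The cost is one clause and a slightly smaller PP set, with the small effect on the standard error shown above. No new data are needed, because informant changes must already be reported.
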